**Fig. 4 Fig4:**
[figure not shown]
Sample size

### Randomization

Health centers in the municipality of Bergen (i.e., health centers agreeing to participate in the study) were randomly allocated to intervention or control groups by researchers involved in the study. Instead of randomization of individuals within health centers, cluster randomization of the primary sampling unit (health centers) was deemed necessary to avoid contamination of information from those in the intervention group to those in the control group while sharing the waiting room of the same health centers.

### Data collection and assessment

#### Data collection instrument

Data will be collected in both phase I and phase II, using a questionnaire intended to elicit parental information about caries and obesity risk behaviors as well as behavioral determinants that will be targeted during the intervention.

The ***first*** part of the interview schedule will assess demographics and socioeconomic status. Demographic data include age, gender, and indicators of socioeconomic and migration status: father’s-mother’s education, occupation, and years of residence in Norway. The ***second*** part of the interview schedule will include parental *knowledge related to* breastfeeding, healthy feeding practices, etiology and prevention of obesity, and dental caries, *attitudes* (food habits, tooth cleaning, regular dental visits), eating habits (sugary food/drinks intake, frequency of consumption of sweet beverages) and different oral hygiene practices. The theory of planned behavior (TPB) will be operationalized according to the practices of the immigrant parents. The ***third*** part of the interview schedule will include information about the parents’ own oral hygiene and dietary habits, cultural traditions, perceived oral health and the utilization of general/dental health services. Finally, the Early Childhood Oral Health Impact Scale (ECOHIS) will be used to measure the quality of life of the children and their families. The ECOHIS is a tool used to analyze the impact of oral health issues on the quality of life of families with children aged between 3 and 5 years [32].

### Outcomes

#### Primary outcome measures

**Change in poor parental knowledge of children’s oral health**

The questionnaires completed by IM before and after a culturally adapted informational intervention will be used to measure the change in parental knowledge. Responses of parents to the first questionnaire, when the child is 0–6 months, and then when the child is 18–24 months were collected. The changes between and within the control and intervention groups will be evaluated.

**Change in poor parental behavior regarding children’s oral health**

The questionnaires completed by IM before and after culturally adapted informational intervention were the basis for measuring the change in parental behavior. Similarly for this outcome, the changes between and within the control and intervention groups will be assessed.

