### Inclusion criteria

#### Phase I

Immigrant parents (IM) of infants (0–6 months old) with NW background (Eastern Europe, Asia, Africa, Turkey, South and Central America) were recruited from different primary health care centers in the municipality of Bergen, Norway. Before the recruitment phase, the health centers were allocated to either intervention or control groups.

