#### Secondary outcome measures caries increment

(a) Clinical examination of caries lesions in the maxillary anterior teeth when the child is 24 months of age. Examination at 6 months is not possible because at this age no teeth have yet erupted. The comparison will be carried out between and within the control and intervention groups. Therefore, examination (duration ~ 15 min) was carried out when the child was 24 months. (b) Caries increments between the ages of 3- and 5-years will be registered from public dental health clinic records. The outcomes for control (N) and the test (IM) groups will be compared.

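### Within-arm change in child-directed behavior starts before the child has teeth, so it is confounded with age; inference should rest on the between-arm comparison

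*Protocol article*

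**What the plan says.** The Outcomes section of the protocol article lists two primary measures, change in parental knowledge and change in parental behavior.

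- **Timing.** It is given under knowledge: "Responses of parents to the first questionnaire, when the child is 0–6 months, and then when the child is 18–24 months were collected".
- **Behavior outcome.** "The questionnaires completed by IM before and after culturally adapted informational intervention were the basis for measuring the change in parental behavior". The next sentence adds: "Similarly for this outcome, the changes between and within the control and intervention groups will be assessed". No ages or items are given for behavior. The ages carry over because the same parents complete the same questionnaires, and Phase I recruits "Immigrant parents (IM) of infants (0–6 months old) with NW background".
- **Questionnaire content** (Data collection instrument). The second part covers knowledge, attitudes, "eating habits (sugary food/drinks intake, frequency of consumption of sweet beverages) and different oral hygiene practices". The third part covers the parents' "own oral hygiene and dietary habits, cultural traditions, perceived oral health and the utilization of general/dental health services".
- **Analysis** (Statistical analysis). A repeated-measures general linear model compares the arms at both time points, and its stated purpose is to obtain intragroup changes. T-tests between arms are also planned.
- **Caries at 24 months** (secondary outcome, part a). "Examination at 6 months is not possible because at this age no teeth have yet erupted". The following sentence says: "The comparison will be carried out between and within the control and intervention groups". Only the 24-month examination is described.

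**The concern.** A before/after change is informative about behavior only if the behavior could have occurred before. At the first questionnaire the child has no teeth and is at most six months old. Brushing the child's teeth, which the intervention demonstrates, has no real baseline then, and intake of sugary food and drink is barely applicable for most such infants. By 18–24 months the child has teeth and eats solid food, whatever the parent was taught. The score on such items will therefore move in both arms for reasons unrelated to the intervention.

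If within-arm change keeps its place as an outcome result, a large and significant change in the intervention arm could be reported as a success when the program did nothing. Sugar items could equally appear to worsen in both arms. The statement that the analysis serves to calculate intragroup changes invites this reading, and the article nowhere warns of the age effect.

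**Working it through.** The plan gives no figure on this point, so there is none to reproduce. Its total of at least 300 (about 50 per center, three centers per arm, hence 3 × 50 = 150 per arm) is used below only to set a scale. The significance level is the stated two-sided 5%. Age shifts, variances and correlations are assumptions, because the article gives none.

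**1. What each contrast contains.** Let M be the age shift common to both arms and d the intervention effect, both in SD units.

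- Expected change, intervention arm: M + d
- Expected change, control arm: M
- Difference between arms: (M + d) − M = d

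With d = 0.25, the effect size in the Sample size section, age accounts for M/(M + d) of the intervention arm's change:

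| M | Share due to age |
|---|---|
| 0.25 | 0.25/0.50 = 50% |
| 0.5 | 0.5/0.75 = 67% |
| 1.0 | 1.0/1.25 = 80% |

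The expected between-arm difference contains no age component.

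**2. How often each test rejects with no intervention effect.** Simulation with d = 0, 150 per arm, SD 1 at both ages, baseline-to-follow-up correlation ρ of 0 or 0.3, no clustering, 2000 runs per setting:

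| M | Within-arm test rejects | Between-arm test of change rejects |
|---|---|---|
| 0 | 4.5–5.0% | 4.6–5.1% |
| 0.25 | 56–73% | 4.7–5.2% |
| 0.5 | 99–100% | 5.2–5.4% |
| 1.0 | 100% | 4.3–5.6% |

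The reason is plain. At ρ = 0 the change has SD √2 = 1.414 and standard error 1.414/√150 = 0.115, so a shift of 0.25 is already about 2.2 standard errors. A larger enrolled number would only raise the within-arm rates.

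**3. Precision of the between-arm contrast.** With two time points, the arm-by-time test in a repeated-measures model is a comparison of change scores. Let k be the baseline SD divided by the follow-up SD. Then

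Var(change)/Var(follow-up) = 1 + k² − 2ρk.

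- Equal variances (k = 1): 2(1 − ρ), which is 2.0 at ρ = 0 and 1.6 at ρ = 0.2.
- Baseline half as variable (k = 0.5): 1.25 at ρ = 0, and 1 + 0.25 − 0.20 = 1.05 at ρ = 0.2.
- Constant baseline (k = 0): 1. Nothing is lost, but the change is then just the follow-up value less a constant.

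Precision is lost only when k > 2ρ, that is, when the baseline varies and is weakly related to follow-up. For equal variances, N = 300, d = 0.25 and no clustering, power is:

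| ρ | Change score | Follow-up only | Follow-up adjusted for baseline |
|---|---|---|---|
| 0 | 0.33 | 0.58 | 0.58 |
| 0.3 | 0.45 | 0.58 | 0.62 |
| 0.5 | 0.58 | 0.58 | 0.71 |

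These figures compare analyses. They do not estimate the trial's power, which also depends on the six clusters.

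**4. Caries at 24 months.** A within-arm change needs two measurements. There is one, and the article says that an earlier one is impossible. The within-group comparison is therefore either not computable or a comparison with zero, which can only show worsening. This step needs no assumption.

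**The case against.** The strongest reply is that this is a randomized trial with a concurrent control arm of the same age. The plan compares changes between arms, and a shared age shift cancels there in expectation, as steps 1 and 2 confirm. This stands. A reader might infer that the primary behavior result mainly measures children growing older, or that the randomized estimate is biased. The documents support neither: the article gives no item scores or expected changes from which such a share could be derived, and the between-arm contrast is sound.

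The reply also has force on the items. The article does not say which items form the behavior score, and the questionnaire is not shown. Tooth cleaning and regular dental visits are listed under attitudes, which parents of a toothless infant can hold. The parents' own hygiene, diet and use of services have a genuine baseline, as does infant feeding. So it cannot be said that every item lacks a before value. The outcome's title, however, refers to behavior concerning the child's oral health, and nothing restricts the score to items that apply at both ages.

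Finally, the variance ratio of 1.6–2.0 assumes equal variances and falls to 1 where the baseline is constant. Choosing follow-up scores over change scores is thus a matter of precision, not validity. Calling the caries wording a stray phrase is also fair, since the valid between-arm comparison stands in the same sentence.

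None of this removes the point that within-arm change is planned as a result, or that it is confounded with age for child-directed items.

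**Conclusion.** The point holds for within-arm change in child-directed items. Its baseline precedes tooth eruption by the article's own account, so it cannot be read as an intervention effect. Under the assumed common shifts of 0.25 to 1.0 SD, age alone makes the within-arm test reject in 56–100% of runs.

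The between-arm contrast keeps its 5% level and is not biased. Its possible cost is precision: up to twice the variance of the follow-up score if variances are equal and the correlation is zero, and none if the baseline is constant. The within-group caries comparison cannot be computed as a change.

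The conclusion rests on carrying the questionnaire ages over from the knowledge outcome, and on the score including child-directed items, as its title indicates. Severity is moderate: a named primary outcome is open to misreading, but the randomized comparison that can answer the question is already planned.

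**What to change.** - **Behavior outcome and Statistical analysis.** Name the between-arm comparison of the 18–24 month behavior score as the primary contrast, accounting for clustering by health center. Adjust for variables already collected at the first interview: knowledge, attitudes, the parents' own oral hygiene and diet, and the child's age at that interview. Age at the follow-up interview is recorded after randomization and should not be treated as a baseline covariate.
- **Within-arm change.** Report it as descriptive only. This includes items that exist at both ages, such as bottle feeding, because they too change as the child grows. Reword the sentence on intragroup changes accordingly.
- **Caries, part (a).** Delete the within-group comparison and compare 24-month caries between arms.

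The cost is rewording and a changed model specification, with no new data. The downside is that the before/after result loses its inferential status.

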#### Secondary outcome measures caries increment

(a) Clinical examination of caries lesions in the maxillary anterior teeth when the child is 24 months of age. Examination at 6 months is not possible because at this age no teeth have yet erupted. The comparison will be carried out between and within the control and intervention groups. Therefore, examination (duration ~ 15 min) was carried out when the child was 24 months. (b) Caries increments between the ages of 3- and 5-years will be registered from public dental health clinic records. The outcomes for control (N) and the test (IM) groups will be compared.

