## Methodology

### Trial Design

This is a cluster randomized controlled intervention follow-up study. By integrating primary health care and the public dental health service, the basis of the study is the application of an early-life intervention program among parents/children of immigrant backgrounds, using the MI technique and CRFA to prevent dental caries and obesity, thereby improving their general health, oral health, and quality of life. Primary care health centers in the municipality of Bergen, Norway, were randomly allocated to intervention or control groups (allocation ratio 1:1), to evaluate the efficacy of the culturally adapted dietary/hygiene advice. The intervention group received guidance on diet/hygiene and the control group received standard care, including regular health information at the primary care health centers. The study has been funded by the Norwegian Research Council for three years.

The study has two phases:

**Phase I (The Intervention Study)** involves assessing oral health-related knowledge, attitudes, and behavior among immigrant parents of infants (0–6 months). It also involves investigating the potential of a culturally adapted oral health education intervention to prevent the development of ECC and to improve parental oral health-related knowledge and awareness (Fig. 1).

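### The follow-up caries outcome, an increment from age 3 to 5 compared between immigrant and Norwegian children, removes any effect present by age 3 and does not estimate the intervention effect

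*Protocol article*

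**What the plan says.** The section on secondary outcome measures (caries increment) lists two caries outcomes.

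- Outcome (a): "Clinical examination of caries lesions in the maxillary anterior teeth when the child is 24 months of age". The contrast is between the randomised arms: "The comparison will be carried out between and within the control and intervention groups". The section explains why there is no earlier examination: "Examination at 6 months is not possible because at this age no teeth have yet erupted".
- Outcome (b): "Caries increments between the ages of 3- and 5-years will be registered from public dental health clinic records". The contrast is different: "The outcomes for control (N) and the test (IM) groups will be compared".

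Other sections bear on what these outcomes are for. Trial Design gives a purpose of Phase I as "investigating the potential of a culturally adapted oral health education intervention to prevent the development of ECC" and places the parents' entry when the child is 0–6 months old. The Abstract says the secondary outcome concerns the impact of the intervention on the children's caries, and the second aim is the effect of the intervention on caries increment. The Hypothesis section predicts a lower lesion count than in the control group. The last aim, and the description of Phase II under Trial Design, speak of caries status rather than increment.

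**The concern.** An increment is a sensible measure when its starting value precedes the intervention. Here the starting value is taken at age 3, more than two years after parents received the guidance. Caries at entry is zero for every child, so the increment since randomisation is simply cumulative caries experience. By starting the count at 3, outcome (b) treats part of the effect as if it were baseline.

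The contrast is a second problem. Outcome (b) is the only caries outcome after 24 months and the only one that covers the whole dentition, yet it is not compared by randomised arm. If the analysis follows the text, the trial will hold whole-mouth caries data at 3 and 5 years on randomised children without using them to answer its own second aim.

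**Working it through.** **Plan's own figure.** There is none for caries. The sample size section (300 participants, effect no smaller than 0.25) is not tied to caries and does not bear on this point. All caries rates below are assumptions chosen to show the mechanism.

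**Step 1: identity.** Write C3 and C5 for cumulative caries at 3 and 5 years. The increment is C5 − C3, so for any two groups:

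difference in increment = difference in C5 − difference in C3.

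Whatever difference exists at age 3 drops out. This needs no assumption about rates.

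**Step 2: additive illustration.** Assume control children acquire a mean of 1 lesion in 0–3 years and 1 in 3–5 years, and the intervention reduces the first period by 30%.

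- No effect after 3: difference at 3 is 0.70 − 1.00 = −0.30; in increment 1.00 − 1.00 = 0.00; at 5 it is 1.70 − 2.00 = −0.30.
- 30% effect in both periods: increment 0.70 − 1.00 = −0.30; at 5 it is 1.40 − 2.00 = −0.60. The increment shows half of the effect.

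**Step 3: limited susceptible teeth.** A tooth spared before 3 can still decay after 3. Assume S = 4 susceptible teeth with per-tooth risk h1 in 0–3 years and h2 in 3–5 years. Then C3 = S·h1 and increment = S·(1 − h1)·h2. The control arm has h1 = h2 = h, and the intervention arm has h1 = 0.7h.

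Worked case, h = 0.50, no effect after 3. Control: C3 = 4 × 0.50 = 2.00; increment = 4 × 0.50 × 0.50 = 1.00; C5 = 3.00. Intervention: C3 = 4 × 0.35 = 1.40; increment = 4 × 0.65 × 0.50 = 1.30; C5 = 2.70.

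Differences, intervention minus control:

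| h | Effect after 3 | At age 3 | Increment 3–5 | At age 5 |
|---|---|---|---|---|
| 0.25 | none | −0.300 | +0.075 | −0.225 |
| 0.50 | none | −0.60 | +0.30 | −0.30 |
| 0.70 | none | −0.84 | +0.59 | −0.25 |
| 0.25 | 30% | −0.30 | −0.17 | −0.47 |
| 0.50 | 30% | −0.60 | −0.09 | −0.69 |
| 0.70 | 30% | −0.84 | +0.16 | −0.68 |

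The intervention arm is better at both ages in every row. The increment has the wrong sign in the first three rows and the last. In the other two it has the right sign but is much smaller than the age-5 difference.

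**Step 4: what the two outcomes cover together.**

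| Caries arising | Maxillary anterior teeth | Other teeth |
|---|---|---|
| Birth to 24 months | (a) | neither |
| 24 to 36 months | neither | neither |
| 3 to 5 years | (b) | (b) |

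**Step 5: the contrast in (b).** Let I, C and N be the mean outcomes in the intervention arm, the control arm and the Norwegian group, and p the share of IM children from intervention centres. The IM mean is pI + (1 − p)C, so

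IM − N = (C − N) + p(I − C).

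The intervention effect I − C is diluted by p and added to the underlying difference between immigrant and Norwegian children. With p = 0.5 (assumed; in line with the 1:1 allocation), an effect of −0.30 enters as −0.15 and cannot be separated from C − N. This holds whether the measure is an increment or a cumulative score.

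**The case against.** The best defence is that the plan has two caries outcomes. A reader might infer that caries is defined only as the 3-to-5 increment, so that an early benefit is lost to the trial. The text does not support that. Outcome (a) compares the arms at 24 months and, starting from no teeth, measures caries from birth in the teeth examined. This stands, and it limits the point to outcome (b) and the gap between the two.

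A reader might also infer that molar caries is never counted. It is: (b) has no tooth restriction, so molar lesions arising at 3–5 years are included. The gap is other teeth before 3, and all teeth from 24 to 36 months.

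Third, the Background defines early childhood caries as running to age 6, so 3–5 years lies within the target condition. That is correct, and it is a reason to count the whole period to age 5, not to omit its first three years.

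Fourth, caries status already appears in the last aim and in the Phase II description. This shows that cumulative status is within the authors' intent, but the outcome definition itself says increment, and the contrast in the Phase II text is again IM against N.

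Finally, sign reversal depends on constructed rates. It does. If the effect persists after 3, the increment keeps the right sign at the low and moderate assumed risks.

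**Conclusion.** The point holds for follow-up outcome (b). Its starting value is post-intervention, so any difference present at age 3 is removed; that is arithmetic. How much is lost is unknown, because the document gives no caries rates. In the assumed cases the increment ranges from half of the age-5 difference, through none of it, to the opposite sign. A reader might infer that a real benefit will vanish or reverse. The document supports only that it can be understated, and that under some assumed rates it reverses.

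Independently of the metric, the IM-versus-N contrast pools the randomised arms and does not estimate the effect set out in the Abstract, Aims and Hypothesis. Replacing increment by status without changing the contrast would not repair this.

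Caries is a secondary outcome, and the primary outcomes on parental knowledge and behaviour are unaffected. The change is worth making because, as written, no whole-mouth caries comparison between the randomised arms is specified.

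**What to change.** Rewrite outcome (b) as follows.

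- Follow-up caries outcome: cumulative caries experience at age 5, with age 3 as a second time point, from the same clinic records.
- Main contrast: intervention against control arm within the IM children, allowing for clustering by health centre.
- Keep IM against N as a separate, descriptive comparison that answers the aims on cultural differences.
- Keep the 3-to-5 increment as a supplementary measure.
- Use the same term for the caries measure in the Aims, Trial Design and Outcomes sections.

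No new examinations are needed. An increment from 3 to 5 presupposes a score at each age, Phase II already places routine examinations at both, and the arm of each IM child is known from Phase I. The article does not name the caries index in the records, so it should be confirmed that a cumulative score can be taken from them. The remaining cost is a small amount of extra analysis on a secondary outcome.

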**Body Mass Index (BMI)**

The BMI of the child will be determined by measuring the height (meter) and weight (Kg) when the child is 5 years old. The control (N) and the test (IM) groups will be compared.

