## Abstract

**Background:**

Immigrants are known to experience greater socioeconomic stress and poorer well-being and to suffer more from lifestyle- and diet-related disorders than native populations. There is also evidence that children of immigrant parents are at greater risk of diverse health problems than their host country cohorts. The aim of this study is to apply and evaluate the efficacy of an early life intervention program among parents/children with immigrant background to prevent childhood caries and obesity, thereby improving the children’s general health, oral health, and quality of life.

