## Hypothesis

We hypothesize that compared to ethnic majority parents in Norway, immigrant parents have poor dietary knowledge, deleterious parental feeding habits and caring behaviors which might trigger caries and obesity among their newborn children. Small children of NW immigrant parents receiving common risk dietary interventions and guidance on hygiene/ feeding practices have better health parameters, including fewer carious lesions, standard BMI, and better quality of life than the control group.

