### Statistical analysis

The data will be analyzed using STATA and SPSS version 24 (SPSS Inc., Chicago, II, USA). Descriptive statistics such as mean and standard deviation for continuous variables and frequency and percentage for categorical variables will be presented. Univariable analysis will be based on cross tabulation and Chi Square statistics. Independent sample t test will be used to assess how sum scores of knowledge, attitudes and the parent’s own oral hygiene and dietary habits varied according to the parents’ age, educational level, and duration of residence in Norway. Differences between intervention and control groups will be analyzed using T-tests and associations will be quantified using eta coefficients. A two-sided significance level of 5% will be applied in all analyses.

Primary analysis will follow an “Intention-to-treat” approach. Comparison between the intervention and control groups at baseline and follow-up to calculate intragroup changes of outcome variables will be performed using generalized linear model (GLM) repeated measures. In the secondary analysis, ‘per-protocol’ approach will be used, where the participants would be excluded if they (1) did not participate in the intervention program, (2) did not complete the questionnaires, (3) were not eligible according to the inclusion and exclusion criteria.

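### The BMI outcome is not tied to 'standard BMI' or to obesity, and a mean difference alone would not show which group has more children in the normal range

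*Protocol article*

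**What the plan says.** The Body Mass Index section under Outcomes contains two statements. The first is the measurement: "The BMI of the child will be determined by measuring the height (meter) and weight (Kg") at age 5. The second is the comparison: "The control (N) and the test (IM) groups will be compared". N stands for native Norwegian and IM for immigrant. The section names no summary statistic, growth reference, z-score, percentile, or overweight or obesity category.

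The Hypothesis section concerns "Small children of NW immigrant parents receiving common risk dietary interventions and guidance on hygiene/ feeding practices" and predicts that these children "have better health parameters, including fewer carious lesions, standard BMI, and better quality of life than the control group". It does not define standard BMI. The abstract's Background states the aim as "to prevent childhood caries and obesity, thereby improving the children’s general health, oral health, and quality of life", and the Trial Design section repeats obesity prevention as a goal.

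The Statistical analysis section is generic. Continuous variables get means and standard deviations, categorical variables get frequencies and percentages, and univariable analysis uses cross tabulation and chi-square. On group contrasts it says: "Differences between intervention and control groups will be analyzed using T-tests". None of these methods is assigned to BMI.

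**The concern.** For a child, a standard BMI and obesity both have meaning only against a reference for age and sex. Standard is also a two-sided target, since a child can miss it by being too heavy or too light. The outcome as defined is a continuous quantity in kg/m², and the one group-difference test named for such a quantity compares means. No BMI category is defined that could be cross-tabulated.

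If the article is followed as it stands, the trial would most naturally report a difference in BMI. That would leave open whether fewer children are overweight and whether more are in the normal range, and a lower mean could be taken as success while more children were underweight. A reference and cut-offs chosen only after the data are in would also be open to selection.

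A second gap sits in the same section. The hypothesis concerns immigrant children who receive the intervention, against a control group, but the comparison stated for BMI is N versus IM.

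**Working it through.** **No plan figure to reproduce.** The article gives no mean, SD, expected difference, overweight rate or sample size for BMI. The figures below are illustrations in SD units, assuming normal distributions. Φ is the standard normal distribution function.

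**1. Does a mean shift say anything about overweight?** Take equal spread (SD 1) and a reference mean of 0. The share above a cut-off c is 1 − Φ(c − mean). The shift of 0.25 SD is the effect size used in the Sample size section; its use for BMI is my assumption.

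- Mean 0: above +1 SD, 1 − Φ(1) = 15.9%; above +2 SD, 2.3%.
- Mean −0.25: above +1 SD, 1 − Φ(1.25) = 10.6%; above +2 SD, 1 − Φ(2.25) = 1.2%.

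So it does, when spreads are similar.

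**2. Does it show which group is closer to standard?** Add the lower tail, Φ(−1 − mean), and the share within ±1 SD. The ±1 SD band only stands in for a normal range.

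| Mean | Above +1 SD | Below −1 SD | Within ±1 SD |
|---|---|---|---|
| +0.25 | 22.7% | 10.6% | 66.8% |
| 0 | 15.9% | 15.9% | 68.3% |
| −0.25 | 10.6% | 22.7% | 66.8% |

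A shift from +0.25 to 0 and a shift from 0 to −0.25 give the same mean difference. The first raises the share in range from 66.8% to 68.3%; the second lowers it from 68.3% to 66.8%. The mean difference does not tell them apart. One has to know where each group sits against a reference.

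**3. Can overweight differ when means do not?** Take equal means, a cut-off at 1.3 SD, and a spread in one group that is 1.2 or 1.3 times the other.

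- Ratio 1.0: 1 − Φ(1.3) = 9.7%.
- Ratio 1.2: 1 − Φ(1.3/1.2) = 13.9%.
- Ratio 1.3: 1 − Φ(1.3/1.3) = 15.9%.

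The expected mean difference is zero throughout. A mean z-score would miss this too, so the case argues for a proportion and not for z-scoring as such.

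**4. The contrast.** Set side by side:

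- Hypothesis: immigrant children given the intervention, against the control group.
- Trial Design: the control group is the standard-care arm, allocated by health centre.
- Abstract, Methods: the secondary outcome is the impact of the intervention on BMI, among others.
- BMI section: N is called the control and IM the test group.
- Inclusion criteria, Phase II: IM are the parents from the intervention study, hence both randomised arms; N are newly recruited at public dental clinics.

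N versus IM is not a randomised contrast and pools the two arms. It cannot test the hypothesis whatever BMI metric is used.

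**The case against.** The strongest reply is that the article does not say raw or mean. Height and weight are also the inputs to a z-score or an overweight category, and the Statistical analysis section lists percentages and chi-square alongside t-tests. The t-test sentence speaks of intervention and control groups, while the BMI section compares N with IM. The reference and cut-offs may be fixed in a full protocol or analysis plan that is not shown. This stands in part. A reader might infer that the trial commits itself to comparing raw BMI means, but the article does not state that, and a standardised or categorical analysis is not ruled out.

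A reader might also infer that a mean difference cannot test the hypothesis or the aim at all. That is too strong: with similar spread, a mean shift moves the overweight share (step 1 of the working). Measuring all children at one nominal age also leaves little age noise for z-scores to remove. The unequal-spread case in step 3 is an assumption, and nothing in the article gives group SDs.

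What the reply does not remove is that the article itself sets the hypothesis, the aim, the outcome and the contrast, and these do not fit together. What standard BMI means belongs to the outcome definition and is more than a modelling detail.

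**Conclusion.** The point holds in a limited form. The outcome is stated only as BMI from height and weight at age 5, and nothing links it to standard BMI or to obesity. A mean difference would be partly informative on overweight but would not by itself show which group has more children in the normal range. In the illustration, one and the same 0.25 SD difference goes with a rise or a fall of about 1.5 percentage points in the share within ±1 SD (66.8% v 68.3%), depending on where the groups start. These sizes rest on assumed normal distributions, assumed cut-offs and an assumed shift; the article offers no BMI data to replace them.

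Independently of the metric, the stated N versus IM comparison does not test the hypothesised effect of the intervention. BMI is a secondary outcome, so this should be corrected but does not touch the primary analysis.

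**What to change.** In the Body Mass Index section:

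- Name one age- and sex-specific growth reference. By its cut-offs, report the proportion overweight or obese and the proportion in the normal range, with the BMI z-score from the same reference as the continuous summary. Define standard BMI in the Hypothesis by that normal range.
- State that the child's sex and exact age at measurement are recorded. The Data collection instrument section lists age and gender without saying whose.
- Make the comparison between the randomised intervention and control arms among immigrant children, accounting for health centre of allocation.
- Keep N versus IM as a separate, descriptive, non-randomised comparison. Health centre as a clustering factor is not defined for N families, who enter through dental clinics, so it should not be carried over to that comparison.

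**Cost.** A minor extra analysis on measurements already planned, plus the two recorded items if they are not collected now. The proportions are less precise than the mean. With 150 per arm (half of the 300 in the Sample size section), a two-sided 5% test, no clustering and no loss to follow-up, power for a 0.25 SD shift is about 58% on the mean. For the matching 15.9% v 10.6% above +1 SD it is about 27%. Clustering and attrition would lower both, so the proportions should be reported with confidence intervals and the z-score kept beside them.
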